**Exhibit 1. ETDRS CHART EQUIVALENT VISUAL ACUITY MEASUREMENTS**

In order to use this ETDRS Chart Equivalent Visual Acuity Measurement Table, it is necessary to obtain the Visual Acuity Score (sum of lines A, B and C on the worksheet). For example if the Visual Acuity Score is 65 letters, the logMAR units would be 0.4. The formula for the conversion is as follows:

logMAR units = 1.7 – (Visual Acuity Score*0.02)

1. **Visual Acuity ( on following page)**

CIRCLE each letter the participant identifies correctly and write the total correct for each row in the column at the right. If the total number of letters read correctly is less than 20, move the participant to a distance of 1 meter from the chart and test the acuity at this distance using only the first six rows of test letters. Prior to actual testing at 1 meter, add a +0.75 sphere to the distance correction in the trial frame.

### I.B FUNDUS PHOTOGRAPHY

***Photographer Experience***

Experimented photographers who have at least 18 months experience at the site of investigation (ophthalmology department of Intercommunal hospital-Créteil) or photographers who have already been certified for fundus and angiography photographs in another study will be authorized to perform photographs.

***Protocol for Study Photographs***

The following procedures establish common standards for the study’s photographic work and will ease efficient reading of digital images. Photographers must send digital images according to these guidelines. Photographers are to send digital images to the LERISS by daily e.mail or by floppy or CD-Rom monthly. Each file should be named correctly.

LERISS staff designed these procedures to allow the study site to use the same file format (file format tiff or may be jpeg format no compression) all along the study. The LERISS Director will approve changes to the protocol only to improve quality or maintain study standards.

LERISS staff recognizes that the nature of Age-related macular degeneration may affect image quality. Photographers’ technical skill and persistence are crucial to securing the images necessary to ensure a valid, valuable study.

***Fundus Photography Procedures***

For each patient, study photographers will take red-free fundus photographs at enrolment and follow-up visits at 6 months and on years 1, 2 and 3 (and at an efficacy end point). The quantification of drusen will be based on these digital images.

The study’s preferred camera is a digital angiograph with 50-degree angle fundus CCD camera (Topcon camera, Topcon 50IA, Tokyo, Japan). In each case, photographers should:

- Use the same CCD camera for all the examinations of a same patient.
- Use image file format : tiff or may be jpeg no compression .

Photographers will take fundus red-free images of the study eye at each patient examination. This study’s protocol does not require stereo. Photographers are to take the macula.

The required field is described below and illustrated on the following page:

Field 2 Monocular image of Macula : macula centered.

***Identifying Photographic Materials***

Fundus red-free photographs will be printed out and archived in the patient’s hospital file. The following data must be written on the printed out photographs: patient number (randomisation number eg: 001) and patient first 3 letters of name and surname, Visit number (from V1 to V5), Date of photography (dd/mm/yy) and Photographer ID, all clearly.

Image files will be duplicate. The photographer will keep the original. Image files will be named correctly as the printed out photographs.

The following data must be mentioned : patient number (randomisation number eg: 001) and patient 3 first letters of name and surname, Visit number (from V1 to V5), Date of photography (dd/mm/yy) and Photographer ID, all clearly.

Each day, after performing the exams, the data will be collected by the study nurse.

***Shipping Photographic Materials***

Photographers should email image files directly to LERISS at the following address.

If it is not possible, they may send these image files by floppy or CD-Rom. In this last case, photographers or their staff should fax a copy of the photography log to the LERISS so LERISS staff are advised of the shipping date.

e.mail:

[[contact]](mailto:[contact])

details:

LERISS (Laboratoire d’Etude et de Recherche en Instrumentation, Signaux et Systèmes)–

**[name]** - [name] - **[contact].

Right Eye

3

**2** x

**1**

**4**

**5**

Left Eye

**1**

X **2**

**3**

**4**

**5**

***Automatic quantification of drusen***

Automatic quantification of drusen is performed using a image enhancement and automatic detection and quantification of drusen software ([name]). The used methods were scientifically validated (see references).

For the automatic quantification, the following steps will be used :

- Image enhancement (grey level histogram enhancement).
- Automatic detection of drusen with sector localization.
- Automatic quantification and classification of drusen (number, size, area) per sector and global.

For evaluation of the drusen evolution, the 2 following steps will be used:

- Geometrical overlaying of images.
- Automatic measurement of variation of drusen number and of area for each drusen.

### I. C DIGITAL FLUORESCEIN AND INDOCYANINE GREEN (ICG) ANGIOGRAPHY

Photographers perform fluorescein angiograms (FA) to document and evaluate changes in Macula (CNV and drusen) that are related to age-related macular degeneration. Photographers will conduct fluorescein angiograms at enrolment and at years 1, 2 and 3 (or at CNV occurrence in between) and ICG angiograms in case of suspicion of CNV occurence. FA will be performed with a digital camera (Topcon 50IA, Tokyo, Japan). ICG will be performed using a scanning laser ophthalmoscope (Heidelberg Engineering, Heidelberg, Germany).

Photographers must NOT perform fluorescein angiography on any patient with a history of an allergic reaction to fluorescein injections or ICG angiography on any patient with a history of an allergic reaction to ICG injections.

Photographers should use the same camera to perform all photographs for a same patient all along the study. This is necessary to be able to compare images between the different visits.

***Fluorescein Injection***

- Inject 5 cc 10% Sodium Fluorescein rapidly (minimum of 1 cc per second) into the ante-cubital vein or a large hand vein with a 21-gauge butterfly needle.

***ICG Injection***

- Inject 5 cc 5% glucose solution of ICG as described for fluorescein.

***Autofluorescence and Fluorescein Sequence***

- Take a **red free** filter photograph of the study eye, as well as a photograph of the non study eye. Be sure to be focus on the retinal vessels on the posterior pole.
- For **Autofluorescence**, take images using the blue light, the barrier, and increasing the intensity of the flash.
- Start timer at the very beginning of the **fluorescein injection.**
- Take early phase photographs of the study eye. Begin photographing about 10 seconds after the start of the injection.
- On the study eye, a minimal number of pictures are required, as follows:
  - 2 pictures on the arterial phase
  - 2 pictures on the early venous phase
  - 2 pictures at the complete filling of retinal veins
  - 3 pictures between 0’40 and 1’00
  - 3 pictures between 1’30 and 2’00
  - 3 pictures between 3’00 and 3’30
  - 3 pictures between 4’30 and 5’00.
- On the fellow eye (affected with choroidal new-vessels) the timing of FA acquisition will be performed as usually required for diagnosis and evaluation of the evolution of the choroidal new-vessels (eg, arterial phase, early venous phase, venous phase, intermediate phase at 1’30 – 2’00 and late phase at 4’30 – 5’00.

***ICG Sequence***

- Take a infra-red filter photograph of the study eye, as well as a photograph of the non study eye. Be sure to be focus on the retinal vessels on the posterior pole.
- Start timer at the very beginning of the injection.

Concerning the study eye:

- Take early phase photographs of the study eye. Begin photographing about 5 seconds after the start of the injection.
- Continue a rapid series of photographs from the beginning of filling of the arterial choroidal vessels until the end of the filling of the venous retinal vessels.
- Following photographs will be performed approximately 5, 15 and 30 minutes after the start of the injection.

For the fellow eye, the procedure will be performed as usually required for evaluation of the evolution of CNV, depending on the stage of the disease: arterial choroidal phase to retinal venous phase, and frames at 5, 15 and 30 minutes after the start of the injection.

***Identifying Photographic Materials***

The printed out photographies that will be archived in the patient file and the image files saved on floppy or CD-Rom must be clearly identified.

The following data must be mentioned patient ID and study number, Visit number, Date of photography and Photographer ID all clearly noted.

### I. D BIOLOGICAL ANALYSES

They will consist in a 12 hour fasting plasma lipid profile and in a measurement of total serum and red blood cell membrane (RBCM) fatty acids.

Blood samples must be taken as follows:

- - 5 ml in a dry tube for plasma lipid profile;
  - 5 ml in a dry tube (with clotting gel) for serum fatty acids
  - 5 ml in a lithium heparin coated tube for RBCM fatty acids.

Blood samples must be transported at ambient temperature and delivered to the laboratory within 5 hours of taking.

The fasting lipid profile will include measurements of total cholesterol (TC) and triglycerides (TG) by enzymatic methods (cholesterol esterase / cholesterol oxydase for TC and lipases for TG) (Roche Diagnostics).

Plasma HDL cholesterol (HDL-C) and LDL cholesterol (LDL-C) will be measured by a direct method: enzymatic staining of plasma lipoproteins separated by electrophoresis (SEBIA).

References :

Benlian P. et al. Comparison of a new method for the direct and simultaneous assessment of LDL and HDL cholesterol with ultracentrifugation and usual methods. Clinical Chemistry 2000; 46: 493-505.

Fatty acids in serum and in RBCM will be measured by gas chromatography after extraction with organic solvents. The extracted free fatty acids will be methylated for 5 minutes with freshly prepared diazomethane; fatty acid methyl esters will be gas chromatographed on a polar capillary column coated with Supelcowax-10-bound phase (i.d. 0;32 mm, length 30 m, film thickness 0.25 m; Supelco, Bellafonte, PA) fitted in a Hewlett-Packard (Palo Alto, CA) gas chromatograph.

Reference :

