# 6. EFFICACY AND SAFETY VARIABLES

## 6.1 Efficacy

### 6.1.1 Evaluation criteria

Primary criterion:

Choroidal neovascularization heralds the onset of exudative macular degeneration, the most severe stage of the disease.

Since this study is designed to evaluate the efficacy of an oral DHA supplementation in the prevention of exudative macular degeneration it is justified to choose the time to occurrence of CNV in the study eye as the main criterion in this study.

The study eye will be the eye not affected with CNV before entering the study.

Secondary criteria:

The ocular criteria will concern systematically the study eye.

- Percentage of patients for whom new vessels occur during the study,
- Change from baseline in visual acuity in LogMar units (ETDRS) and proportion of patients with a visual acuity decrease from baseline of more than 15 letters at ETDRS,
- Change from baseline in visual function (assessed with a multifocal ERG),
- Occurrence and progression of drusen (number, size, and area) ,

all criteria allowing to determine the efficacy of the treatment to slow-down the progression of the disease.

- DHA concentration changes in red blood cell membrane is a surrogate marker for DHA ability to penetrate the retina visual cells.

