### 6.1.2 Examination schedule

The different visits will take place on D0, Month 6 (15 days), Year 1( 30 days),

Year 2 (30 days) and Year 3 ( 30 days).

Before inclusion, a baseline assessment will take place on D0. Besides validating the inclusion and exclusion criteria, this baseline visit will also enable the recording of demographic (including ethnicity) and baseline data. Data concerning some identified risk factors for AMD, as age and history of addiction to smocking, will be recorded. Moreover a diet questionnaire must be completed in order to assess the patient’s fish intake frequency.

Any general pathology (particularly diseases predisposing to bleeding or haemorrhage) and ocular pathology as well as any concomitant treatment will be recorded.

These data will be updated all along the study.

For patients previously supplemented with omega-3 fatty acids the corresponding stopping date will be recorded.

On each visit, ophthalmic assessments will include the following:

- Best corrected visual acuity measured with ETDRS charts
- Slit Lamp Examination
- Multifocal ERG (except on 6 month visit)
- Fundus photographs
- Fluorescein angiography (except on 6 month visit)

Moreover a complete profile of blood lipids will be performed on D0, at the 6 month visit and at the 3 year visit : fasting plasma lipoproteins [triglycerides (TG), total cholesterol (TC), HDL-C and LDL-C ] and fatty acids in serum and in red blood cell membranes (RBCM) will be measured. To this end 15 ml of venous blood will be collected after a 12 hour fasting period (as described in appendix I.D).

These data will allow first to evaluate for each patient the compliance to the treatment (DHA level in plasma) and the efficacy of DHA to penetrate the cell membrane (DHA level in RBCM), then to confirm the safety of the treatment concerning the metabolism of lipoproteins (fasting plasma lipoprotein profile).

Moreover since TC is considered as a risk factor for age-related macular degeneration, it will be considered for evaluation of treatment efficacy.

Furthermore, as previously mentioned (see section 4.2), apoE genotype of consenting patients will be evaluated on DNA of white blood cells, on D0.

10 ml of venous blood will be collected. The protocol for extraction of DNA from white blood cells and for evaluation of apoE allele is given in appendix I.E. If appropriate, the efficacy of the treatment will be assessed considering the apoE genotype .

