### Secondary efficacy variables

Fundus photographs (red free frame), performed through the dilated pupil, will allow :

- first to describe the type, number, size and area of drusen on D0,
- then to evaluate the occurrence and progession of drusen (number, size and area), in the study eye, at each follow-up visit.

For this purpose, an automatic quantification of drusen will be performed by LERISS laboratory using an image enhancement and automatic detection and quantification of drusen software. The protocol for quantification and evaluation of evolution of drusen is described in appendix I. B.

Change in visual acuity will be evaluated from baseline using the ETDRS charts. Best corrected visual acuity will be evaluated, before pupil dilatation, by the same person at each visit. The protocol for evaluation of visual acuity is given in appendix I. A.

A significant decrease in visual acuity is defined as a decrease of more than 15 letters at ETDRS.

Multifocal ERG modification from baseline will be evaluated yearly on the study eye. ERG responses will be obtained from the anesthetized cornea, through the dilated pupil, with a bipolar contact lens electrode (see appendix I.G). ERG must be performed before fundus photographs and angiography.

DHA concentration in red blood cell membranes (RBCM) will be performed on D0, at the 6 month visit and at the 3 year visit. For this purpose, 5 ml of 12 hour fasting blood samples will be taken in the early morning. DHA concentration change in red blood cell membrane is considered as the witness of the DHA ability to penetrate the retina visual cells*.* The protocol for dosage of fatty acids in RBCM is given in appendix I.D.

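### Appendix I.D announces total fatty acids but describes methylating free fatty acids only after extraction, so the assay as written would miss the membrane-bound DHA that a secondary criterion relies on

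*Protocol*

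**What the plan says.** Protocol Appendix I.D opens by stating what will be assayed: "measurement of total serum and red blood cell membrane (RBCM) fatty acids". It then gives the method in two steps. The first is "Fatty acids in serum and in RBCM will be measured by gas chromatography after extraction with organic solvents". The second is "The extracted free fatty acids will be methylated for 5 minutes with freshly prepared diazomethane", after which the methyl esters are chromatographed. No other preparation of the fatty acids is described.

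Section 6.1.3 makes this the governing method for the red-cell measure: "The protocol for dosage of fatty acids in RBCM is given in appendix I.D".

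The body of the protocol also says what the measure is for. Section 6.1.1 lists it among the secondary criteria: "DHA concentration changes in red blood cell membrane is a surrogate marker for DHA ability to penetrate the retina visual cells". Section 6.1.3 repeats the idea: "DHA concentration change in red blood cell membrane is considered as the witness of the DHA ability to penetrate the retina visual cells". Section 6.1.2 uses it to show that DHA gets into the cell membrane. Section 8.1 plans a between-group comparison of the increase at 6 months and at 3 years, by Student t-test or Wilcoxon test. Section 5.3 presents serum DHA, which goes through the same assay, as a good indicator of compliance.

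**The concern.** DHA that has become part of a cell membrane is esterified in phospholipid. An assay meant to show incorporation has to split it out before it can be read as a methyl ester. The appendix names the free acids as the species that is methylated and names no step that frees the rest.

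If the laboratory worked to the text, the red-cell criterion would report a different quantity from the one it is named for. The randomised comparison would still be a fair comparison of whatever was measured, because both arms go through the same assay. It would not, however, answer whether DHA had entered the membrane. This is the trial's only measure of uptake into cells. If the CNV result were null, it is also the measure that would help separate a supplement that did not reach the tissue from one that reached it and had no effect.

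**Working it through.** The plan gives no figure to reproduce, so the check is a comparison of texts plus one point of general chemistry.

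1. **Analyte announced.** Appendix I.D speaks of total fatty acids in serum and of red-cell-membrane fatty acids. The word for total may attach to serum alone or to both. Read either way, the serum assay is meant to cover more than the free fraction. The red-cell assay is meant to reflect membrane content, as sections 6.1.1, 6.1.2 and 6.1.3 make plain.

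2. **Species methylated.** Appendix I.D names only the free fatty acids in the extract.

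3. **What the written steps do.** This is general chemistry, not a statement in the protocol. Solvent extraction recovers intact lipids without splitting them. Diazomethane methylates free carboxylic acids and does not convert fatty acids bound as esters in phospholipids, triglycerides or cholesterol esters. So the two steps as written yield methyl esters from the unesterified fraction.

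4. **Search for a release step.** No hydrolysis, saponification or transesterification of the fatty-acid samples appears in Appendix I.D or anywhere else in the protocol.

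5. **Level of detail nearby.** For this same assay, Appendix I.D gives the methylation time, the column's diameter, length and film thickness, and the instrument maker. For cholesterol and triglycerides it names the ester-splitting enzymes. Appendix I.E names the protein digestion used in extracting DNA. Comparable release steps are therefore written down for other assays but not for this one.

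6. **Result.** Steps 1 and 2 do not agree, and by step 3 the difference is between the free fraction and the membrane-bound quantity that the criterion is named for.

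7. **Reach.** Blood for fatty acids is taken at D0, month 6 and year 3 (sections 6.1.2 and 6.3). With 248 patients at full attendance, 248 × 3 = 744 red-cell samples and 744 serum samples. This counts the samples exposed to the problem. It does not measure the error in any of them.

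8. **What is not touched.** The primary analysis is a log-rank test of time to CNV (section 8.1), and the sample size rests on 3-year CNV risks of 15% and 30% (section 8.2). The assay enters neither.

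**The case against.** The strongest reply is that the appendix is a short summary and that silence is not omission. It does not say that hydrolysis is left out. It also names no step for separating red cells or isolating their membranes, and nobody would conclude that these are skipped. The free fatty acids in the extract could be acids freed during a preparation that is not spelled out, with the detail held in a laboratory procedure. This stands in part: the protocol cannot show what is done at the bench. It does not remove the conflict, because the text does more than leave a step unmentioned. It names as the methylated species one that does not match the announced analyte.

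A reader might go further and infer that the criterion will certainly fail to measure membrane DHA. The protocol does not support that, for the reason just given.

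A reader might also take the title of the cited method paper, "Sphingolipids and cholesterol modulate membrane susceptibility to cytosolic phospholipase A2", as a sign that a free-fatty-acid assay was intended. A title does not show what the paper's methods section does, and the paper is not at hand, so nothing rests on it.

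Two further limits on the stakes are fair. Serum DHA is not the only compliance measure: section 5.3 also requires return of empty blister-packs and unused capsules, with good compliance set at 80% or more of capsules taken. And section 2 reports that an earlier study at 480 mg per day of DHA, with EPA, raised serum and red-cell-membrane levels. That is context only, since the assay used there is not described.

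**Conclusion.** The point holds conditionally. Appendix I.D contradicts its own stated analyte. Followed as written, it would read the unesterified fraction rather than the DHA incorporated in membrane phospholipid. This rests on the general chemistry of diazomethane and on the text being followed literally. If the laboratory already uses a release step, the fault is confined to the wording.

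The numerical size of the error cannot be given. The protocol states no unesterified fraction for red-cell membranes or serum, and any percentage would be a guess. A reader might also infer that serum free fatty acids after the 12-hour fast are a poor guide to recent capsule intake. Nothing in the protocol supports or refutes that. The serum point is only that the free fraction is not the total that the appendix announces.

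The consequences are limited to one tested secondary criterion and one of two compliance measures. The matter should be settled before samples are assayed, but it does not threaten the primary result.

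**What to change.** Amend Appendix I.D so that esterified fatty acids are released before gas chromatography, for both serum and red-cell membranes. This can be hydrolysis of the extracted lipids ahead of methylation, or direct transesterification in place of the diazomethane step. If a release step is already in use, write it in. State that the result is expressed as DHA in total fatty acids of the serum or membrane. Require the same procedure at D0, month 6 and year 3, so that changes from baseline compare like with like.

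The cost is a change to the appendix and, if the step is not already done, one routine laboratory step on blood that is drawn anyway. No extra blood, visit or patient is needed.
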